#### Other study parameters

Preoperative factors that could be associated with postoperative complications will be recorded, these include: age, sex, body height, body mass, body mass index, nutritional status, smoking status, location and type of the tumor, presence or absence of metastases, CPET parameters other than the VAT, WHO performance score, ASA score [77], Charlson comorbidity index [59], type of surgical resection, muscle strength, and the TUG test.

### Safety

All adverse events reported spontaneously by participating patients, or observed by the investigator or his staff will be recorded.

### Data analysis

#### Sample size calculation

Nowadays, there is 33% 30-day morbidity and 3.8% 30-day mortality in patients undergoing colorectal surgery in the Netherlands [3, 78]. We expect the high-risk group (patients with a VAT < 11 mL/kg/min) to have a morbidity rate of 50%. Dunne et al. stated that a 10% improvement in cardiorespiratory fitness would move 30% of the patients from high to low operative risk [25, 28]. Robinson et al. [34] showed that 21% of the non-frail colorectal patients had a postoperative complication, versus 40% in the pre-frail group and 58% in frail patients. We hypothesized a complication rate of 20% in the prehabilitation group.

For the sample size calculation we used the computer program PS Power and Sample Size Calculations version 3.0, January 2009 (Copyright © 1997-2009 by William D. Dupont and Walton D. Plummer) [79, 80]. Using an alpha of 0.0492 (due to one interim analysis) and a power of 0.80, we need 39 patients in each group to find statistically significant results. Taking into account 10% dropout, we need 43 patients in each group.

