#### Statistical analysis

Nominal variables will be presented as numbers with percentages. Continuous variables will be presented as mean ± SD, or as median and interquartile range, as appropriate. Data will be presented in tables and figures. All tests will be performed on the intention to treat population, and on the per-protocol population. Data distribution will be checked with help of an epidemiologist.

For categorical variables, chi-squared tests or Fisher’s Exact tests, as appropriate, will be performed to analyze the difference between the intervention and control group. For continuous variables this will be done by independent samples t-tests or Mann-Whitney U tests, as appropriate. A repeated measurements analysis (mixed models in SPSS) will be performed to assess changes over time in continuous variables. A cost-effectiveness analysis will be performed, with the use of quality adjusted life years. Withdrawn patients will be followed by checking the patient’s data file. We will use the intention-to-treat analysis to avoid various misleading artifacts.

When half of the patients needed that are calculated (43 patients) are included, a blinded independent data analyst will perform an interim analysis with a stopping rule according to O’Brien-Fleming [81]. If this interim analysis shows a significant difference in postoperative complications between the prehabilitation group and the usual care group (at *P* < 0.0054), this data analyst will contact the Medical Ethics Committee, and debate the outcome of the interim analysis and its eventual repercussions. Thereupon this committee will advise the principle investigator of the research team (JK) to decide to stop the inclusion in case of superiority. If the interim analysis shows no or minimal difference (< 10% on overall complications), the study will be stopped due to futility. Because of the interim analysis, the final *P*-value that is considered to be significant is reduced to *P* < 0.0492.

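### The interim and final thresholds (0.0054 and 0.0492) have the O'Brien-Fleming shape for one look at half the patients, but their constant is slightly too low for an overall two-sided level of 0.05

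*Protocol article*

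**What the plan says.** The Statistical analysis section fixes the timing of the look: "When half of the patients needed that are calculated (43 patients) are included". The total is 2 × 43 = 86, so this is half. A data analyst "will perform an interim analysis with a stopping rule according to O’Brien-Fleming". Superiority at the look requires a significant difference "between the prehabilitation group and the usual care group (at *P* < 0.0054"). At the end, "the final *P*-value that is considered to be significant is reduced to *P* < 0.0492".

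The Sample size calculation section uses the same final level, "Using an alpha of 0.0492 (due to one interim analysis) and a power of 0.80", and arrives at 39 patients per group, or 43 after an allowance for dropout.

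The article does not state the overall type I error or whether tests are two-sided. The Statistical analysis section also says that the study will stop for futility if the interim difference in overall complications is below 10%.

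**The concern.** The final level is lowered only to keep the overall type I error at its nominal value after the extra look. If the two stated levels do not add up to that value, the adjustment misses its purpose.

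For one look at half the information, the O'Brien-Fleming levels for a two-sided 0.05 are 0.0052 and 0.0480. The stated final level of 0.0492 is more lenient. A final P between 0.0480 and 0.0492 would therefore count as significant, although the named method at 0.05 would not allow it. These are explicit decision thresholds for the primary endpoint, so they are not a detail that can be assumed to sit in another document.

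**Working it through.** **Inputs.** From Statistical analysis: one look at 43 of 86 (information fraction t = 0.5), interim level 0.0054, final level 0.0492. From Sample size calculation: 50% versus 20%, power 0.80, 39 per group. Assumed: two-sided tests and an overall level of 0.05. The article implies 0.05 by saying "Because of the interim analysis, the final *P*-value that is considered to be significant is reduced to" 0.0492.

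**1. Reproduce the plan's sample size.** The formula for two proportions with pooled variance and no continuity correction is

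n = [z(1−α/2)·√(2p̄(1−p̄)) + z(0.80)·√(p₁(1−p₁) + p₂(1−p₂))]² / (p₁−p₂)²,

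with p₁ = 0.50, p₂ = 0.20 and p̄ = 0.35. At α = 0.0492, z = 1.967 and n = 38.67, so 39 per group, as stated. A one-sided calculation gives 31. This supports the two-sided reading.

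**2. Check the shape.** With a look at half, O'Brien-Fleming sets the interim boundary at c·√2 and the final boundary at c.
- Interim level 0.0054 corresponds to z = 2.782.
- Final level 0.0492 corresponds to z = 1.967.
- The ratio is 2.782/1.967 = 1.4145, against √2 = 1.4142.

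The pair therefore has the O'Brien-Fleming shape for a look at half, with c = 1.967.

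**3. Total type I error of the stated pair.** Under the null hypothesis, Z₁ and Z₂ are bivariate normal with correlation √0.5.
- P(|Z₁| > 2.782) = 0.0054.
- P(|Z₁| ≤ 2.782 and |Z₂| > 1.967) = 0.0459.
- The total is 0.0054 + 0.0459 = 0.0513.

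A simulation with 10 million draws gives 0.0512. Over the rounding of both thresholds the total runs from 0.0512 to 0.0514, so rounding does not explain the excess.

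**4. Constant for a total of 0.05.** Solving for c gives 1.977, with boundaries 2.797 and 1.977. The levels are 0.0052 and 0.0480.
- If 0.0054 is kept, the final level must be 0.0479.
- If 0.0492 is kept, the interim level must be 0.0026.
- The O'Brien-Fleming-type spending function gives 0.0031 and 0.0490.

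**5. Sensitivity to the information fraction.** Taking 43 of 78 evaluable patients (t = 0.551), the total is 0.0510. The look is triggered by inclusion while the endpoint needs 30 days after surgery, so fewer than half the outcomes may be available. At t = 0.40 the total is 0.0520.

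**6. Effect on the sample size.** At α = 0.0480 the same formula gives n = 38.97, still 39 per group. Power at 39 per group is 80.0% instead of 80.3%.

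**7. What the normal approximation leaves out.** The primary comparison is a 2×2 table, tested by chi-squared or Fisher.
- At 39 per group, no table has a P-value between 0.0480 and 0.0492 under either test.
- At 43 per group, a few do, for example 13 versus 22 by chi-squared (P = 0.0482) and 13 versus 23 by Fisher (P = 0.0485).
- At the look (22 and 21 patients), no table falls between 0.0052 and 0.0054.
- The exact total for the stated pair, over common rates of 20% to 50%, is about 0.026 to 0.033 with Fisher and about 0.045 to 0.055 with chi-squared.

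**8. Binding futility.** With 21.5 patients per arm and a pooled rate of 35%, the standard error of the difference is √(2 × 0.35 × 0.65/21.5) = 0.145. A difference below 10 points then means |Z₁| < 0.69. If the trial always stops there, the total falls to about 0.047.

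**The case against.** The strongest case on the other side has four parts.

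- **The stated pair is O'Brien-Fleming in form.** This stands. A reader might infer that the thresholds come from another method or a mistimed look, because the pair totals 0.05 only at an information fraction of 0.70. The documents do not support that. The ratio of the z-values is √2 to rounding, which is what a look at half requires. Only the constant is off.
- **The 0.05 target is never stated.** This also stands, so it has to be labelled an assumption. It is a safe one: the final level is described as reduced because of the look, two-sided testing reproduces 39 per group, and nothing suggests that 0.0513 was intended.
- **0.0513 is not the error rate of the tests that will be run.** This stands. Discreteness moves the actual error by more than 0.0013, in either direction with chi-squared and well downward with Fisher. At exactly 39 per group the corrected final level would change no decision.
- **The futility rule is worded as mandatory, and if binding it brings the total to about 0.047.** The arithmetic is right. However, the article derives its levels from the O'Brien-Fleming rule and one interim analysis, not from the futility stop. Efficacy levels are usually set without credit for futility, so that the error stays controlled if the trial continues past that stop.

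Together these points make the matter minor, but none of them makes 0.0492 the right level for the named rule at 0.05.

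**Conclusion.** The point holds as a small error of calibration. The stated pair uses an O'Brien-Fleming constant of 1.967 where 1.977 is needed, and gives a total two-sided type I error of about 0.0513, an excess of about 0.0013. This rests on an assumed overall two-sided level of 0.05, a look at half the information, a non-binding futility stop and the normal approximation.

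A reader might go further and conclude that the trial's real error rate exceeds 0.05 or that its sample size is wrong. Neither follows. The real rate depends on the test chosen and on how the futility stop is applied, and the sample size is unaffected. What remains is a narrow window of final P-values, 0.0480 to 0.0492, in which the stated threshold and the named method disagree. Some tables at 40 to 43 per group fall in that window.

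**What to change.** Replace 0.0054/0.0492 with 0.0052/0.0480 in the Statistical analysis section, and 0.0492 with 0.0480 in the Sample size calculation section. State the overall two-sided level as 0.05. If the look has already been taken at 0.0054, the matching final level is 0.0479.

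Alternatively, name an O'Brien-Fleming-type spending function, which gives 0.0031/0.0490 at half, and recompute the final level from the number of outcomes actually available at the look. This also covers a look that does not fall exactly at half.

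The cost is a change to three numbers and a slightly stricter final threshold. With 0.0052/0.0480 the sample size remains 39 per group, and power goes from about 80.3% to 80.0%.

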#### Procedures for data checking and entering

Data (coded on study code) will be entered in the Statistical Package for the Social Sciences for Windows (SPSS, version 23.0, IBM, SPSS Inc., Chicago, IL, USA). All data are held in an encrypted format and will be stored in a secured locked room. All variables will be checked for the number of missing, impossible or improbable values, prior to statistical analysis. In case of improbable or impossible values, the patient’s data file will be checked by the data manager. Descriptive statistics will be calculated for all variables, and distributional assumptions will be checked. The study coordinator, chief investigator, and a blinded data analyst will have access to the final trial dataset. Due to the low risk nature of the intervention, the Medical Ethics Committee determined that a data monitoring committee is not required.

#### Statistical analysis

Nominal variables will be presented as numbers with percentages. Continuous variables will be presented as mean ± SD, or as median and interquartile range, as appropriate. Data will be presented in tables and figures. All tests will be performed on the intention to treat population, and on the per-protocol population. Data distribution will be checked with help of an epidemiologist.

For categorical variables, chi-squared tests or Fisher’s Exact tests, as appropriate, will be performed to analyze the difference between the intervention and control group. For continuous variables this will be done by independent samples t-tests or Mann-Whitney U tests, as appropriate. A repeated measurements analysis (mixed models in SPSS) will be performed to assess changes over time in continuous variables. A cost-effectiveness analysis will be performed, with the use of quality adjusted life years. Withdrawn patients will be followed by checking the patient’s data file. We will use the intention-to-treat analysis to avoid various misleading artifacts.

When half of the patients needed that are calculated (43 patients) are included, a blinded independent data analyst will perform an interim analysis with a stopping rule according to O’Brien-Fleming [81]. If this interim analysis shows a significant difference in postoperative complications between the prehabilitation group and the usual care group (at *P* < 0.0054), this data analyst will contact the Medical Ethics Committee, and debate the outcome of the interim analysis and its eventual repercussions. Thereupon this committee will advise the principle investigator of the research team (JK) to decide to stop the inclusion in case of superiority. If the interim analysis shows no or minimal difference (< 10% on overall complications), the study will be stopped due to futility. Because of the interim analysis, the final *P*-value that is considered to be significant is reduced to *P* < 0.0492.

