### Participants

To be eligible to participate in this study, a patient must meet all of the following inclusion criteria: 1) ≥ 60 years, 2) colorectal cancer or premalignant colorectal lesions (dysplasia grade I, II, or III) requiring colorectal resection, 3) undergoing elective colorectal resection at Medisch Spectrum Twente, Enschede, or at Ziekenhuisgroep Twente, Almelo, 4) having a life expectancy of more than 6 months as estimated by the surgeon, 5) has given informed consent to participate in this study, 6) a metabolic equivalents of task (MET) score ≤ 7 on the veterans-specific activity questionnaire (VSAQ), 7) able to perform a CPET, 8) a VAT < 11 mL/kg/min as measured at the baseline CPET, and 9) willing to perform prehabilitation at a community physical therapy practice in the adherence area of both hospitals. All patients not meeting these criteria will not be considered for inclusion. Participants can leave the study at any time for any reason if they wish to do so, without any consequences. The investigator can decide to withdraw a participant from the study for urgent medical reasons.

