### Randomization

To analyze the effect of a three-week prehabilitation program on postoperative complications, patients with a VSAQ score ≤ 7 will be randomized in the intervention group (prehabilitation) or the control group (usual care) by using block-stratified randomization [37]. Randomization is stratified by disease and treatment type: 1) patients with colon cancer, 2) patients with rectal cancer who will receive one week of neoadjuvant radiotherapy, and 3) patients with rectal cancer who will receive five weeks of neoadjuvant chemoradiotherapy. The clinical research coordinator of the surgical department will be responsible for the randomization. Participants, care providers, and outcome assessors will not be blinded after randomization. However, the data analysts will be blinded to group allocation and are independent to the intervention. After randomization, all participants will perform a CPET for final inclusion, as merely patients with a VAT < 11 mL/kg/min can participate in the study.

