**Table 2 Tab2:** Content of the three-week peripheral resistance training program^a^

	Repetitions^b^	Duration	Intensity^c^
Week 1, session 1, 2, and 3	3 × 8 repetitions	20 min	70% of 1RM
Week 2, session 4, 5, and 6	3 × 8 repetitions	20 min	76% of 1RM
Week 3, session 7, 8, and 9	3 × 8 repetitions	20 min	82% of 1RM

^a^: Peripheral resistance training of the large muscle groups of the lower and upper extremities using open and closed kinetic chain exercises (without physical therapy equipment or machines): crouching by means of squat exercises (primary muscle group: quadriceps femoris; secondary muscle groups: gluteal muscles, hamstring muscles, and gastrocnemius muscle), pulling by means of pulley exercises (primary muscle groups: latissimus dorsi muscle and rhomboid muscles; secondary muscle groups: biceps brachii muscle, rotator cuff, and trapezius muscle), pushing by means of pulley exercises (primary muscle group: pectoral muscles; secondary muscle groups: shoulder muscles, triceps brachii muscle), and lifting by means of pulley exercises (primary muscle groups: trunk muscles and shoulder muscles; secondary muscle groups: quadriceps femoris, gluteal muscles, and trapezius muscle)

^b^: Rest intervals of 60-90 s between each set of repetitions

^c^: Based on the 10RM, the patient’s 1RM was determined using the Oddvar Holten diagram

Abbreviations: 1RM, one-repetition maximum; 10RM, ten-repetition maximum

Patients with colon cancer or dysplasia will participate in the prehabilitation program in the time between contemplation of surgery and the procedure, whereas patients with rectal cancer, in case neoadjuvant therapy is needed, will complete the physical exercise training program *prior to* radiotherapy (in case of neoadjuvant radiotherapy, 5 × 5 Gy) or in the twelve-week period *after* neoadjuvant chemoradiotherapy (training in the last three weeks before surgery).

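### The primary test ignores the randomisation strata, and the listed strata leave out some eligible patients; a stratified test needs no extra patients but changes power only modestly

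*Protocol article*

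**What the plan says.** Protocol article, Randomization: allocation is block-stratified. "Randomization is stratified by disease and treatment type: 1) patients with colon cancer"; the second and third strata are rectal cancer with one week of neoadjuvant radiotherapy and rectal cancer with five weeks of neoadjuvant chemoradiotherapy. The cardiopulmonary exercise test follows randomisation, and patients whose ventilatory anaerobic threshold (VAT) is 11 mL/kg/min or more then leave the trial.

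Participants, criterion 2, admits "colorectal cancer or premalignant colorectal lesions (dysplasia grade I, II, or III) requiring colorectal resection". Prehabilitation program describes the training windows and puts dysplasia with colon cancer, "whereas patients with rectal cancer, in case neoadjuvant therapy is needed", follow a different timetable. That condition implies that some rectal cancer patients have no neoadjuvant therapy.

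Statistical analysis: for categorical variables, chi-squared or Fisher's exact tests, "as appropriate, will be performed to analyze the difference between the intervention and control group". The 30-day complication endpoint, which is sized as a proportion, falls under this sentence. No stratum or covariate is mentioned for it.

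Sample size calculation: "Using an alpha of 0.0492 (due to one interim analysis) and a power of 0.80, we need 39 patients in each group", and then "Taking into account 10% dropout, we need 43 patients in each group".

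**The concern.** Two things do not fit together.

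First, the design blocks on three groups and the named test then disregards them. When blocking holds within prognostic strata, part of the outcome variation cannot contribute to the difference between arms. A pooled test still counts that variation in its standard error, so it rejects too seldom under the null and can lose power. When patients are removed after randomisation, blocking no longer guarantees balance within strata, and the pooled test does not correct a chance imbalance.

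Second, the three-item list does not cover the eligible population. A stratified analysis cannot be run on everyone until each patient has a stratum, and the article does not say where the unlisted patients go.

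What is at stake is precision and a complete analysis set, in a trial whose planned power is only just 0.80.

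**Working it through.** **1. The plan's own figure.** The inputs are a control risk of 50% ("We expect the high-risk group (patients with a VAT < 11 mL/kg/min) to have a morbidity rate of 50" per cent), an intervention risk of 20% ("We hypothesized a complication rate of 20% in the prehabilitation group"), alpha 0.0492, power 0.80 and 1:1 allocation. Sidedness is not stated; two-sided without continuity correction gives the published number:

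n = [z(α/2)·√(2·p̄·q̄) + z(β)·√(p₁q₁ + p₂q₂)]² / (p₁ − p₂)²

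= [1.967·√(2·0.35·0.65) + 0.842·√(0.25 + 0.16)]² / 0.30² = 38.7, so 39 per group.

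Power at 39 per group is 0.803. Also 39 × 1.1 = 42.9, which gives the stated 43. Sizing and test are therefore both unstratified, with no margin on the 78 evaluable patients.

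**2. Why the pooled test can be conservative.** With blocking intact, the null variance of the difference is governed by the average within-stratum variance, while the pooled test uses p̄(1 − p̄). Take assumed shares of 50/25/25% and null risks of 0.27, 0.69 and 0.77 (odds ratios 1, 6, 9; mean 0.50):

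- within-stratum: 0.50·0.27·0.73 + 0.25·0.69·0.31 + 0.25·0.77·0.23 = 0.196
- pooled: 0.50·0.50 = 0.25
- ratio 0.196/0.25 = 0.785, square root 0.886
- effective critical value 1.967/0.886 = 2.22, two-sided size about 0.026

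The simulated value for this case is 0.031. Incomplete blocks and small numbers account for the difference.

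**3. Simulation at 78 patients.** Permuted blocks of 4 within strata, overall risks 50% against 20%, alpha 0.0492, 8,000 runs per row (6,000 where half were dropped). CMH is the Cochran-Mantel-Haenszel test without continuity correction. Shares, block size and stratum odds ratios are assumptions.

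| Shares; stratum odds ratios | Size pooled | Size CMH | Power pooled | Power CMH |
|---|---|---|---|---|
| 75/15/10; none | 0.056 | 0.055 | 0.808 | 0.806 |
| 75/15/10; 1.5, 2 | 0.053 | 0.052 | 0.806 | 0.807 |
| 75/15/10; 3, 4 | 0.046 | 0.049 | 0.815 | 0.830 |
| 75/15/10; 6, 9 | 0.040 | 0.051 | 0.816 | 0.858 |
| 50/25/25; 1.5, 2 | 0.051 | 0.051 | 0.806 | 0.808 |
| 50/25/25; 3, 4 | 0.044 | 0.052 | 0.822 | 0.840 |
| 50/25/25; 6, 9 | 0.031 | 0.050 | 0.823 | 0.872 |
| Half dropped at random, 75/15/10; none | 0.052 | 0.047 | 0.804 | 0.794 |
| Half dropped at random, 75/15/10; 6, 9 | 0.044 | 0.051 | 0.822 | 0.866 |

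**4. Simulation at 86 patients.** Treatment odds ratio 0.25, shares 70/15/15 or 60/20/20, blocking intact:

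| Control risks by stratum | Power pooled | Power CMH |
|---|---|---|
| 50/50/50% | 0.849–0.851 | 0.843–0.846 |
| 47/53/58% | 0.846–0.847 | 0.841–0.842 |
| 45/55/70% | 0.833–0.841 | 0.837–0.845 |
| 35/60/80% | 0.742–0.759 | 0.779–0.792 |

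Pooled size with prognostic strata and intact blocking was 0.031–0.035 in one set of runs, but 0.042–0.044 at the milder 45/55/70% pattern. After random exclusions it was about 0.043–0.046, within an overall 0.040–0.047 in another set.

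**5. Continuity correction.** At 78 patients with blocking intact, CMH with the correction has power 0.724–0.734 (no or moderate stratum effects), 0.757–0.767 (strong) and 0.791–0.805 (very strong). That is below the pooled chi-squared test in every row.

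**6. Coverage of the strata.**

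| Eligible group | Training timetable | Stratum listed |
|---|---|---|
| Colon cancer | Given | Yes |
| Dysplasia | Given, with colon cancer | No |
| Rectal, radiotherapy | Given | Yes |
| Rectal, chemoradiotherapy | Given | Yes |
| Rectal, no neoadjuvant therapy | Implied only | No |

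**The case against.** The best defence is that nothing here is invalid. The pooled test does not materially inflate type I error, it matches the sample size calculation, and stratum adjustment is often left to a statistical analysis plan that is not shown. The benefit depends wholly on how prognostic the strata are, and the article reports no complication risk by stratum. With non-prognostic or mildly prognostic strata the stratified test gains nothing and may lose half a point to a point. Two strata could hold only about 13 to 17 patients each (15 to 20% of 86). All of this stands, and it limits the size of the point. It does not remove it: the article names a test that departs from its own randomisation, and its list of strata omits eligible patients.

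A reader might infer three stronger things that the documents do not support.

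- That the strata were chosen because they predict complications. The Randomization section gives no reason, and the different training windows suggest a logistical one.
- That unlisted patients are allocated ad hoc. The article does not say how they are allocated. Since dysplasia shares the colon cancer timetable, the first stratum is its natural home.
- That stratifying is more accurate at no cost. It can cost about a point of power, and more if a continuity correction is used.

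**Conclusion.** The point holds as a modest one. The primary comparison as written does not use the randomisation strata, and the list of strata is incomplete. The consequence is possible conservatism, not bias or excess false positives. Size falls to about 0.03–0.035 only with clearly prognostic strata and intact blocks. The design excludes patients on VAT after randomisation, which makes about 0.043–0.046 the more relevant figure. Moving to CMH without continuity correction changes power by about −1 point (0.804 to 0.794: no stratum effect, half dropped) to about +5 points (0.823 to 0.872: very strong effects).

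These figures rest on assumed stratum shares, stratum risks and blocks of 4, and on exclusions that are random with respect to arm and outcome. The article gives no values for any of these.

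**What to change.** Before the final unblinded analysis, prespecify as primary a Cochran-Mantel-Haenszel test **without continuity correction**, stratified by the strata as actually used at randomisation. Report a stratum-weighted risk difference with its 95% CI, and keep the pooled chi-squared test as a sensitivity analysis.

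In the Randomization section, state in which stratum patients with dysplasia, and patients with rectal cancer and no neoadjuvant therapy, were and will be placed, so that the stratified test covers everyone. Enrolment began in February 2014, so this can only document practice; it cannot change allocations already made.

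Cost: one sentence in each of two sections. The 39 and 43 per group stay as they are and no new data are needed. The price is a loss of up to about one point of power if the strata turn out not to be prognostic.

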#### Charlson comorbidity index

The Charlson comorbidity index [59, 60] will be scored at baseline for the prehabilitation group and usual care group. It can be a useful preoperative tool in predicting morbidity and mortality outcomes in patients with colorectal cancer [61].

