### Study outcomes

#### Primary study parameter

The primary study parameter is the number of overall postoperative complications within 30 days after surgery in the prehabilitation group and usual care group. Complications will be divided in surgical and non-surgical complications. Surgical complications will be scored as anastomotic leakage, perineal wound complication, rectal stump abscess, intra-abdominal abscess, fistula, sepsis, ileus, abdominal wound complication, intestinal necrosis, stoma complication, urological complication, bleeding, iatrogenic intestinal injury, or iatrogenic vascular injury. Non-surgical complications will be scored as cardiovascular, pulmonary, thromboembolic, renal, or neurological. Complications will be recorded and graded by using the Clavien-Dindo classification [75, 76]. Readmissions within 30 days will also be recorded.

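### The arm comparison uses none of the recorded baseline predictors; adjusting for one or two would add a modest amount of power that depends on a prognostic strength the article does not give

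*Protocol article*

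**What the plan says.** The primary parameter is "the number of overall postoperative complications within 30 days after surgery in the prehabilitation group and usual care group". The sample size treats it as a proportion, 50% under usual care and 20% with prehabilitation. For categorical variables, the Statistical analysis section states that chi-squared or Fisher's exact tests, as appropriate, "will be performed to analyze the difference between the intervention and control group". It names no covariates.

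Elsewhere the article collects variables that it regards as prognostic:

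- Other study parameters: "Preoperative factors that could be associated with postoperative complications will be recorded". The list includes age, ASA score and Charlson comorbidity index.
- Charlson comorbidity index, scored at baseline in both groups: "It can be a useful preoperative tool in predicting morbidity and mortality outcomes in patients with colorectal cancer".
- Questionnaires: frailty is measured at baseline with the Groningen frailty indicator.
- Sample size calculation: a cited study found complications in 21% of non-frail, 40% of pre-frail and 58% of frail colorectal patients.

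The article uses the geriatric assessment for prediction only. No variable is assigned to adjusting the treatment comparison.

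**The concern.** The trial is small. At the planned rates it expects 39 x 0.50 + 39 x 0.20 = 27.3 events in 78 patients, so a chance imbalance in age or comorbidity can move the estimate noticeably. Adjusting for a baseline variable that predicts the outcome removes part of that noise without a single extra patient. This matters because the Discussion reports that inclusion is challenging. Randomisation is stratified by disease and treatment type only, so neither the allocation nor a test stratified in the same way would use age or comorbidity. At stake are a few points of power and an estimate less exposed to chance imbalance.

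**Working it through.** **Inputs** (Sample size calculation): 50% v 20%; "Using an alpha of 0.0492 (due to one interim analysis) and a power of 0.80". The stated result is 39 per arm. Sidedness is not stated; two-sided reproduces the figure.

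**1. The plan's own number.** n = [z(alpha/2) x sqrt(2 x 0.35 x 0.65) + z(beta) x sqrt(0.25 + 0.16)]^2 / 0.30^2 = [1.967 x 0.6745 + 0.8416 x 0.6403]^2 / 0.09 = 38.7, so 39 per arm. Power at 39 is 80.3% by formula and 80.2% exactly for the uncorrected chi-squared test. Fisher's test, which the article also allows, has 73.2%.

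**2. Approximate gain from adjustment.** Multiply the variance by (1 - R2), where R2 is the share of outcome variance explained by the covariates. The unadjusted null standard error is sqrt(0.455/39) = 0.1080, and the alternative one is sqrt(0.41/39) = 0.1025. Power = Phi[(0.30/sqrt(1 - R2) - 1.967 x 0.1080)/0.1025].

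| Assumed R2 | Power, 39 per arm |
|---|---|
| 0 | 80.3% |
| 0.05 | 82.4% |
| 0.10 | 84.4% |
| 0.15 | 86.5% |

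Exactly 85% needs R2 of about 0.114, a covariate AUC of about 0.70.

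**3. What the article itself supports.** Its only outcome gradient by a baseline factor is frailty, 21/40/58%. With equal thirds the mean is 0.397 and the between-group variance is (0.187^2 + 0.003^2 + 0.183^2)/3 = 0.0228. R2 is then 0.0228/(0.397 x 0.603) = 0.095, and power 84.2%. Frailty mixes that average about 50% complications give R2 of 0.03-0.09 and power of 81.7-84.0%.

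**4. Simulation** (39 per arm, marginal rates held at 50% and 20%, alpha 0.0492). Chi-squared power is 79-81% throughout.

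| Assumed AUC | Linear model, 1-2 covariates | Linear model, 3 covariates | Logistic likelihood-ratio, 3 covariates |
|---|---|---|---|
| 0.50 (no value) | about 80% | 79.7% | 81.4% |
| 0.63 | 81-83% | 79.9% | 81.4% |
| about 0.70 | 84% | 83.3% | 84.6% |
| 0.74 | 86% | 85.0% | 86.7% |

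The three-covariate columns rest on 6,000 runs each, a simulation error of about sqrt(0.8 x 0.2/6000) = 0.5 of a point.

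**5. Type I error at the final analysis** (nominal 4.92%). The linear model with one or two covariates gives 4.6-5.4%. The three-covariate logistic likelihood-ratio test gives about 5.4-6.5%, so part of its apparent gain is inflation: it shows 81.4% even when the covariates carry no information.

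**6. Interim analysis** (43 patients, about 43 x 0.35 = 15 events, P < 0.0054). Under the null, the three-covariate logistic likelihood-ratio test rejects in about 1.1% of trials, roughly double the nominal 0.54%. A separate run gave 0.94-1.00%, against 0.38-0.54% for chi-squared.

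**The case against.** A chi-squared test of a binary outcome is valid and consistent with the sample size. The article promises to record these factors, not to adjust for them. The full analysis plan is not shown and may contain an adjusted model. All of this stands, and a reader who took the unadjusted test for a mistake would be going too far. The point survives because the article does fix a method for the arm comparison, and that method leaves precision unused. If an unseen plan adjusts, the two need to be reconciled.

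The prognostic strength is unknown. The article gives no AUC or R2 for age or Charlson, frailty is not one of the two covariates proposed here, and entry restrictions may narrow the spread of risk. This stands too: the gain has to be given as a range that includes zero.

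The 80% baseline assumes the full 10% dropout. Withdrawn patients are followed through their files, and with all 43 per arm analysed, unadjusted power is already 84-85%. That is correct. The step 2 formula then moves from 84.1% to 86.0%, 87.8% and 89.6% at R2 of 0.05, 0.10 and 0.15, so the increment is similar but less needed.

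Baseline VAT looks like an obvious covariate. However, Recruitment and Randomization place the CPET after allocation, with participants and care providers unblinded. Table 3 marks a CPET at enrolment but puts the VAT result after allocation. VAT is also range-restricted by entry below 11 mL/kg/min. The objection to using it is accepted.

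**Conclusion.** The point holds as a modest, conditional improvement. With one or two prognostic covariates, power at 39 per arm would rise from about 80% to about 81-86% for an assumed AUC of 0.63-0.74. The frailty gradient points to about 82-84%, as an indication of scale only. If the covariates are not prognostic, nothing is gained.

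Two stronger readings are not supported. A reader might infer that adjustment delivers 85% power; that needs an R2 of about 0.114, which nothing in the article establishes. A reader might also infer that adjustment repairs the selection that occurs when final inclusion follows randomisation. It does not: it balances measured covariates only and leaves the selection mechanism as it is.

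**What to change.** Amend Statistical analysis before the data are opened:

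- Name as the primary analysis a covariate-adjusted risk difference with its confidence interval, from a linear model or a standardised estimate with a test valid in small samples. This keeps the 50% v 20% scale.
- Adjust for age and Charlson comorbidity index, the latter scored from comorbidity documented before allocation.
- State that the P-value from this model decides the trial at P < 0.0492, and keep the chi-squared test as supportive.
- Do not use the three-covariate logistic likelihood-ratio test. Leave out baseline VAT, and type of resection, which is final only after allocation.
- State the interim test: either the chi-squared test at P < 0.0054 or the same linear model.

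If the randomisation strata are also to enter the model, settle that at the same time, since about 27 events support few terms.

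The cost is wording and a slight loss of simplicity, with no gain if the covariates prove weak. No new data or patients are needed.
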